##### Process evaluation

The purpose of the process evaluation is to assess both feedback report uptake and intention to change behavior. This component of our evaluation will assess whether staff read and understood the report and whether they intend to change a particular behavior that was targeted on the feedback reports. As in DICE-LTC, about a week after we distribute the feedback reports, we will ask employees to complete a survey to assess their response to the feedback reports. Staff will self-report on whether they received the report, whether they read the report, how they might use the feedback reports, whether they intend to use the information from the report to change care practices, and what sorts of changes they might consider making to their care practices as a result of the reports. All of these questions relate to feedback report uptake. The final section of the survey was constructed to capture intention to change behavior in pain assessment practice, according to the constructs described in a manual on survey development using the Theory of Planned Behavior [24,25]. This section will be completed by the direct care provider staff only. Surveys will be conducted in a room, away from client/resident care and activity. All surveys will be anonymous. We will ask some demographic information, including the office/site they work in and their years of experience in HC/SL settings. This is similar to the tool that was used in DICE -LTC, with only wording revised to suit the HC/SL environment. After completing the survey, each employee will also be offered a $5 Tim Horton's gift certificate in appreciation for their participation.

We will deliver the surveys to the sites during a time they are already meeting for another purpose. We will provide a self-addressed return envelope for returning the surveys to the research team. Our site champions are instrumental in the implementation of this study. Site champions will distribute the feedback report and survey to all employees who are not in attendance at the time of in-person report distribution using their usual mail distribution system. Those absent employees will review the feedback reports and complete the survey and return it to the research team in the self-addressed envelope provided.

In addition, we will conduct several 45-minute focus groups with regulated and unregulated healthcare providers at selected sites to further explore and verify the quantitative findings from the post-feedback surveys. The intention of the focus groups is to delve deeper into how the respondents felt they understood the reports and their perceptions of report utility. We will conduct the focus groups with 5 to 10 healthcare providers per group, which will take place after the report/survey distribution in the third quarter. The focus groups will use a semi-structured discussion format. We will derive the questions to stimulate discussion based on our preliminary survey data from the first two quarters, discussing in more depth several variables that were addressed in the quantitative analysis related to the perceptions of the feedback reports.

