## Methods

The overall intervention evaluation uses a controlled interrupted time-series design with quarterly feedback reports in the seven HC offices and 11 SL sites across Alberta. Follow-up surveys to assess uptake of the audit-with-feedback intervention will be offered to all participating employees one week after feedback report distribution. The purpose of the follow-up survey is to assess staff response to the feedback reports and their intent to change their behavior based on what they learned from the feedback. We will not be measuring actual change in behavior through the surveys but rather their *intent *to change their behavior. This is similar to the survey tool that was used in the Data for Improvement and Clinical Excellence--Long-Term Care (DICE-LTC) study, with only wording revised to suit the HC/SL environment. A sample survey instrument can be found in Additional File 1.

We will use in-person audit and feedback in two zones and electronic distribution in two zones. This will be more fully described later in this protocol paper.

The process evaluation will be conducted concurrently with the prospectively collected survey data and will consist of observation, focus groups, and self-report measures to assess uptake of the feedback reports. We define uptake as reading the feedback reports, discussing with colleagues and managers, and reporting some degree of intention to change behavior based on the reports. Observation will occur in the sites where we deliver the feedback reports in person. The focus groups will be targeted sessions based on the findings of the observations and the self-report survey and will be held in four of the participating sites.

We received ethics approval from the University of Alberta Health Research Ethics Board, panel B. We obtained operational approval for all sites from all participating study organizations. Participation by staff is voluntary and will not affect their employment in any way.

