Once every three months (*i.e*., every quarter), two research assistants (RAs) will hand deliver the report to all employees present and available at each site during the time he or she is there. The reports are specific to the HC or SL site, and all direct care providers and managers within these sites are targeted to receive the report that gives them information about how the clients in their site compare to the other sites in the study on the selected indicator areas. Additional copies will be left in a central location, and staff will be told that they are welcome to take one later if they would like. The RAs will stay for about one hour after distributing reports to answer any questions or take comments. One of the RAs will also passively observe what employees do with the reports after receiving them and will discretely note how many times the employees read the reports, discuss them with others, discuss with the RA, or other actions such as throwing the reports away. No names or identifying information will be noted. We will use a simple check sheet as well as write narrative notes about the specific observations. This is the basis for our field notes and will be used in conjunction with staff self-report on the post-feedback survey to obtain an estimate of report uptake. At the end of the site visit, we will also post flyers reminding staff that we will be conducting surveys the following week.

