#### Procedures for electronic feedback report distribution

We will follow the same order as with North and Central zones described above, but rather than in person, we will distribute feedback reports and conduct the post-feedback report survey electronically. We will use the continuing care desktop (CCD), a tool developed by the Centre for Health Evidence in collaboration with Alberta Health and Wellness that is available to all employees in continuing care throughout the province of Alberta [26]. Access to the CCD is through individual log-in privileges managed through the workplace. We plan to post the feedback reports by site on the CCD, with a separate notice emailed to the site leader. The notice will include a poster that the site leader will be asked to print and post in at least three prominent locations to notify the employees to review the feedback report on the desktop. One week later, we will follow the same procedure with the site leader with a poster notifying the employees that the feedback report follow-up survey is available for them to complete. The participating employees will log onto the CCD, where they will see a link to complete the online survey. By using an electronic distribution mechanism, we will be able to compare, descriptively, how electronic feedback reports compare to in-person feedback reports. As well, comparisons on distribution for post-feedback report surveys will also be made between in-person and electronic formats.

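### Staff absent from the in-person visit appear to get the feedback report and the uptake survey together, against the plan's own one-week interval

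*Protocol article*

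**What the plan says.** The opening of Methods in the protocol article states the general rule. Follow-up surveys "will be offered to all participating employees one week after feedback report distribution".

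The rule is repeated for both delivery modes:
- In-person zones, Process evaluation: "about a week after we distribute the feedback reports, we will ask employees to complete a survey".
- In-person zones, Procedures for feedback report generation and distribution: at the end of the report visit, "we will also post flyers reminding staff that we will be conducting surveys the following week".
- Electronic zones, Procedures for electronic feedback report distribution: "One week later, we will follow the same procedure with the site leader with a poster".

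For staff who miss the in-person visit, Process evaluation gives a separate procedure. "Site champions will distribute the feedback report and survey to all employees who are not in attendance at the time of in-person report distribution", using the site's internal mail. It continues: "Those absent employees will review the feedback reports and complete the survey and return it to the research team", in an envelope that is supplied.

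The same section lists what the survey measures: "Staff will self-report on whether they received the report, whether they read the report". It also covers how they might use the report and whether they intend to change practice. A final part on intention, about pain assessment, is for direct care staff only. Methods makes reading the report the first component of uptake.

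**The concern.** A survey meant to show whether staff read a report should not itself cause them to read it. With a week between the two, most reading recorded on the survey will have happened without it. If both arrive together, and looking at the report comes just before filling in the form, a returned survey no longer separates staff who would have read the report anyway from those who read it because a form was waiting. Intention has a similar problem: for these staff it is taken at some other, unstated time after exposure than for their colleagues.

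The uses at stake are:
- research question 2, on how provider groups respond to the reports;
- the comparison of in-person with electronic distribution, which is one of the article's two stated reasons for using both modes;
- to a lesser degree, the dose predictor in the Analysis section, which draws partly on self-reported reading.

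The mailed route exists only at in-person sites, so any distortion from it falls on one side of the mode comparison.

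**Working it through.** The article states no attendance, response or uptake rate, so there is no figure to reproduce. The check sets the passages side by side and then shows how the size would depend on unknown inputs.

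**Step 1: interval between report and survey, by group**
- All participating employees (Methods): one week.
- In-person sites, general (Process evaluation, and the flyers at the report visit): about one week.
- Electronic sites: one week between the report notice and the survey notice.
- In-person sites, staff absent from the visit (Process evaluation): none stated. One sentence names report and survey together, with one sender and one mail route. The next sentence has the employee review, complete and return.

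The last group is the only one without an interval.

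**Step 2: what the survey measures.** It asks about receipt and reading of the report and about intention to change. If it arrives with the report, the survey task can produce a yes on reading, and intention is recorded at a different delay.

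**Step 3: who is affected.** Only staff at in-person sites (North and Central zones) who miss the visit. The electronic procedure has no mailed report and survey.

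**Step 4: how the size would scale.** Let *a* be the share of in-person survey respondents who were absent from the visit. Let *d* be the extra proportion of them who read the report because the survey came with it. The rise in self-reported reading among in-person respondents is *a* × *d*. Neither input is in the article, so the values below are assumptions:
- *a* = 0.20, *d* = 0.10: 0.20 × 0.10 = 0.02, or 2 points.
- *a* = 0.20, *d* = 0.30: 0.20 × 0.30 = 0.06, or 6 points.
- *a* = 0.50, *d* = 0.10: 0.50 × 0.10 = 0.05, or 5 points.
- *a* = 0.50, *d* = 0.30: 0.50 × 0.30 = 0.15, or 15 points.

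If few staff miss the visits, *a* falls below 0.20 and the effect shrinks in proportion. The calculation is per returned survey. The dose predictor is defined per member of staff, so these points do not carry over to it directly.

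**The case against.** The strongest reply is that the article never says report and survey travel in one mailing. A site champion could mail the report on the visit day and the survey a week later. Every sentence would then hold, including the one-week rule for all participating employees. That is possible, and it is why the point rests on the natural reading and not on an explicit statement. But nothing in the text says the two are separated, and the sentence on what absent staff do reads as a single sequence. If staggered mailing is intended, the passage still needs to say so. Nor is this a detail left to a fuller document: the article describes the procedure for absent staff, and the description does not agree with its own rule.

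Other parts of the reply stand and limit the point:
- **Number of absent staff.** A reader might infer from the dispersed workforce that many are absent. The article does not support this. It mentions dispersal to explain why visits are timed for when most staff are on site.
- **Large inflation.** A reader might assume that nearly every absent respondent reads only because of the survey, and so arrive at a very large shift. No figure in the article supports that, nor the idea that intention is recorded within minutes of reading.
- **Dose predictor.** Someone who reads because a survey arrived has still been exposed. For the dose that is real reading, not error.
- **Electronic sites.** Report and survey link sit on the same desktop system, and nothing says the report is taken down. A survey poster can therefore prompt late reading there too. Spare copies left at in-person sites can do the same. The contrast between modes is one of degree, and the comparison is descriptive only.
- **Other evidence.** Observation and focus groups also inform uptake, and no difference in bias between provider groups has been shown.
- **The survey form.** The instrument is in an additional file that is not shown. It cannot be said to instruct staff to read the report, or to lack an item on how the report was received.

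**Conclusion.** The point holds as an internal conflict with a plausible measurement consequence. On its natural reading, the procedure for absent staff drops the one-week interval that the article sets for everyone. For those staff in the North and Central zones, the survey can prompt the reading it records, and intention is measured at a different time after exposure. Self-reported uptake in those zones may be raised, and the in-person versus electronic comparison may tilt towards in-person delivery.

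The size is unknown. The 2 to 15 point range rests entirely on assumed values for the share of absent respondents and the extra reading prompted. It shows scale and is not an estimate.

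The effect on the dose predictor is secondary: prompted reading is real exposure, although it would partly reflect the survey procedure and how many staff attend at each site. RAI-HC client outcomes are not directly affected. A reader might go further and conclude that in-person uptake is invalid or that the primary analysis is compromised; the article supports neither.

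**What to change.** Reword the Process evaluation section so that the site champion mails the report to absent staff at the time of the visit, and mails the survey with its return envelope about one week later, alongside the on-site survey. This applies the article's own interval to everyone.

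Make sure the anonymous form records how the report was received: handed over, mailed, taken from the spare copies, or not received. Without such a mark, mailed respondents cannot be picked out afterwards. With it, uptake and intention can be shown with and without mailed staff, including in the comparison with electronic sites.

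The cost is one more internal mailing per quarter for the site champions and one item on the form. A few returns from absent staff may be lost, because a survey sent separately may be easier to set aside. If staggered mailing was always intended, the change to the procedure is one clarifying sentence.

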#### Procedures for electronic feedback report distribution

We will follow the same order as with North and Central zones described above, but rather than in person, we will distribute feedback reports and conduct the post-feedback report survey electronically. We will use the continuing care desktop (CCD), a tool developed by the Centre for Health Evidence in collaboration with Alberta Health and Wellness that is available to all employees in continuing care throughout the province of Alberta [26]. Access to the CCD is through individual log-in privileges managed through the workplace. We plan to post the feedback reports by site on the CCD, with a separate notice emailed to the site leader. The notice will include a poster that the site leader will be asked to print and post in at least three prominent locations to notify the employees to review the feedback report on the desktop. One week later, we will follow the same procedure with the site leader with a poster notifying the employees that the feedback report follow-up survey is available for them to complete. The participating employees will log onto the CCD, where they will see a link to complete the online survey. By using an electronic distribution mechanism, we will be able to compare, descriptively, how electronic feedback reports compare to in-person feedback reports. As well, comparisons on distribution for post-feedback report surveys will also be made between in-person and electronic formats.

### Analysis

Our primary analysis, using time series with and without adjustment for covariates, including site-level context data from the ACT survey, will allow us to assess change in the client outcomes that are reported in the feedback report over time. For the primary analysis for this study, we will pool the RAI-HC data from all study sites, using RAI-HC data for six months prior to the intervention, during the intervention, and for six months after the intervention. We will assess changes in trends seen before, during, and after the intervention period for the client outcomes included in the feedback reports (pain, delirium, negative mood, falls, visits to hospital within previous 90 days) and other outcomes not included in the reports (*e.g*., pressure ulcers, incontinence, and social engagement). For the purpose of the time-series analysis, the quarterly data will be converted to monthly measures of aggregate client outcomes across all sites. Predictor variables will include the intervention dose, operationalized as the proportion of staff who were observed or who self-reported reading the reports. Data for control facilities will be requested and analyzed at the end of the post-surveillance period.

Qualitative data from the focus groups and from the narrative observation notes will be coded into themes, including specific barriers and facilitators to feedback report uptake. At the site level, these findings will be used alongside the post-feedback report survey data, the client outcome data, and the findings from the ACT tool to glean additional detail around contextual differences that may explain possible variations in responses to the feedback reports across sites.

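### The intervention dose mixes anonymous, unlinkable sources, has an extra counting route in the in-person zones only, and sits without a defined role in the primary-analysis paragraph

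*Protocol article*

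**What the plan says.** The Analysis section describes the primary analysis as "time series with and without adjustment for covariates, including site-level context data from the ACT survey". It pools RAI-HC data from all sites into monthly aggregate measures, covering six months before, the intervention year, and six months after. The same paragraph adds "Predictor variables will include the intervention dose", which it defines as "the intervention dose, operationalized as the proportion of staff who were observed or who self-reported reading the reports".

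The two sources of that dose are described elsewhere in the article:

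- **Observation.** Methods says "Observation will occur in the sites where we deliver the feedback reports in person". Under Procedures for feedback report generation and distribution, an assistant will "discretely note how many times the employees read the reports", along with other actions, and "No names or identifying information will be noted". That section says the notes and the survey will be used together to estimate uptake.
- **Self-report.** The Process evaluation section has staff state, about a week after each report, whether they received and read it. It adds "All surveys will be anonymous".
- **Mode by zone.** North and Central receive reports in person, Calgary and South electronically. For the electronic zones, "The participating employees will log onto the CCD, where they will see a link to complete the online survey". No observation is described there.

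**The concern.** A proportion of staff who meet either of two criteria needs the number of distinct people who meet at least one of them. One source here counts events and neither carries an identity, so a person seen reading who also returns a survey cannot be recognised as the same person. This is settled when the data are collected, so a later analysis plan cannot repair it.

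The definition also means different things in different zones, because one of its two routes exists only where delivery is in person. A dose-response estimate would then partly compare delivery modes, and with them zones, rather than levels of reading.

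Finally, staff choose whether to read. Sites where staff engage with reports may improve for other reasons. A dose coefficient therefore does not answer the first research question, which concerns the effect of the reports. The article does not say how dose relates to the before, during and after terms that do address it.

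**Working it through.** The article gives no dose figure, so there is none to reproduce. All values of A, B, t, r, o and quarterly dose below are assumptions.

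**1. Can the union be identified?** Let A be the share of staff observed reading and B the share self-reporting reading, on one staff denominator. Without linkage, all that is known is

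max(A, B) ≤ share in either ≤ min(1, A + B).

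| A | B | Lower bound | Upper bound | Width |
|---|---|---|---|---|
| 0.2 | 0.2 | 0.20 | 0.40 | 0.20 |
| 0.4 | 0.5 | 0.50 | 0.90 | 0.40 |
| 0.5 | 0.5 | 0.50 | 1.00 | 0.50 |

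With A and B each between 0.2 and 0.5, the width equals the smaller of the two, so it runs from 0.2 to 0.5. A is itself uncertain, because the observer counts how often reports are read, not how many people read them.

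**2. Is dose comparable between modes?** Let t be the true share reading, r the survey response, and o the share of readers seen by the observer, with r and o independent. Non-responders count as not reading.

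- Electronic dose = t × r
- In-person dose = t × [1 − (1 − r)(1 − o)]
- Gap = t × (1 − r) × o

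With t = 0.6 and the same r in both modes:

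| r | o | Electronic | In person | Gap |
|---|---|---|---|---|
| 0.7 | 0.2 | 0.420 | 0.456 | 0.036 |
| 0.5 | 0.4 | 0.300 | 0.420 | 0.120 |
| 0.3 | 0.6 | 0.180 | 0.432 | 0.252 |

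Reading is identical in every row, so the gap is measurement alone. These in-person values are the favourable case, since they assume the de-duplication that step 1 shows is impossible.

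**3. What could a dose term add to the pooled series?** The series has 6 + 12 + 6 = 24 monthly points. Surveys follow four report rounds, so there are at most four measured dose values, and pooling removes differences between sites.

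Take a segmented model with an intercept, a trend, and a level and slope change at the start and at the end of the intervention. That is six columns, and dose is a seventh. Set dose to 0 outside the intervention year.

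- Constant dose: rank 6 of 7, exactly collinear.
- Quarterly doses 0.6, 0.5, 0.55, 0.4: rank 7 of 7, but only about 1.4% of the variance of dose is left unexplained by the other six columns.
- Wider swings, 0.3, 0.6, 0.4, 0.5: rank 7 of 7, about 9% left.

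Dose therefore carries little information beyond the period terms unless reading swings widely between quarters.

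**The case against.** The strongest reply is that this is a condensed article. The combined figure is offered only as an estimate, and the denominator and combining rule can wait for a fuller document. The denominator can indeed wait. The missing link between anonymous sources cannot, and neither can the absence of observation in two zones.

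Several stronger readings are tempting, and the article does not support them:

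- **That no dose can be computed.** Each survey asks about reading, so a self-report proportion is available in all zones and the union can be bounded. If the definition's or means alternative measures, the self-report one works as it stands. Only the person-level union fails.
- **That dose replaces the effect of delivering reports.** The primary analysis examines trends before, during and after the intervention, and is also run without covariates. The text does not say whether dose enters both versions, is added to the period terms, or serves as the exposure term. The role is unclear, but it is not shown to be wrong.
- **That dose is exactly collinear with the period terms.** This needs a constant dose. Four unequal values break it, although strong overlap can remain.
- **That the in-person versus electronic comparison is biased by this variable.** That comparison is described as descriptive, and nothing says it uses the combined dose.
- **That online respondents are mostly readers.** Report and survey share one log-in desktop, which makes this plausible. It is inference, since no response data are given for either mode.

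**Conclusion.** The concern holds in this limited form. As worded, the dose at in-person sites can only be bounded, with an interval 0.2 to 0.5 wide over the assumed range. It is also not comparable between modes. At equal true reading (60%) and equal survey response, the in-person figure is higher by 0.04 to 0.25. If response differs between modes, the size and even the direction of the gap can change, but the dependence on mode remains. Because mode follows zone, it cannot be separated from geography.

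A coefficient for this variable would be an uptake association, not the effect of delivering reports. In the pooled series it rests on about four values that overlap heavily with the period terms. The unadjusted primary analysis may be unaffected. The wording should be changed, but the flaw does not invalidate the primary design.

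**What to change.** 1. State that the primary effect is estimated from the intervention-period (report delivery) terms, without dose.
2. Define dose from the one source available in every zone: self-reported reading in the post-report survey, per site and quarter.
3. Report it both among respondents and over eligible staff, with the response rate by delivery mode. Neither version is enough alone. Counting non-responders as non-readers carries response differences into dose: with 60% true reading everywhere and response of 70% in person and 30% online (assumed), dose is 0.6 × 0.7 = 0.42 against 0.6 × 0.3 = 0.18, a gap of 0.24. The respondents-only figure avoids this but is biased if readers are more likely to respond.
4. Use dose only in a secondary site-quarter dose-response analysis that adjusts for or stratifies by delivery mode, and interpret it as an association.
5. Report the assistants' observations descriptively and keep them out of dose.

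The cost is a change of wording and a quarterly staff head-count from each site. The drawback is a less favourable uptake figure that is still imperfect, because it rests on self-report and on who returns the survey.
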